#### Arm 3: MRI-guided stereotactic LITT group

After local anesthesia, skull markers will be implanted and then a CT scan will be performed, and the results of which will be fused with T1-weighted MRI by the Sinoplan (V2, Sinovation, China) software for robot navigation registration. After general anesthesia, the patient’s head will be fixed with a magnetic resonance compatible head frame and connected to the operating table and SR1 stereotactic robot (Sinovation, China). After registering the surgical plan, the surgical field will be sterilized, the skull will be drilled, the dura will be punctured, and a probe will be used to ensure smooth access to the fiber-optic cannula. The guide screw will be installed, the cooling jacket containing the fiber will be placed at the planned depth, and an MRI scan will be performed to determine the location of the fiber. After confirming that the position of the optical fiber is in line with the plan, a series of ablations will be performed with real-time visualization using MRI thermometry to ensure that target structures reached temperatures between 60 and 80 °C. If necessary, the optical fiber will be withdrawn for repeated ablation. After all ablations are completed, the scope of ablation will be determined by scanning enhanced nuclear magnetic resonance. Then, the laser fiber, cooling catheter, and anchor bolt will be removed, the skin will be closed, and the patient will be awakened.

### Outcomes

#### Primary outcome

The primary outcome is the participant’s seizure remission rate, which was defined by the following formula:$$\mathrm{Seizure\,remission\,rate}=\frac{\mathrm{Baseline\,seizure\,frequency}(\mathrm{per\,month}) -\mathrm{ Post}-\mathrm{op\,seizure\,frequency }(\mathrm{per\,month})}{\mathrm{Baseline\,seizure\,frequency}(\mathrm{per\,month})}\times 100\%$$

#### Secondary outcomes

Engel classification at one-year follow-up after surgery.The proportion of participants with neurologic impairment after surgery, primarily determined by the change in NI.SHH scale score at each post-operative visit and neurological physical examination findings at each post-operative visit.Spectrum distribution and Epileptogenic Index change of video EEG at each post-operative visit.Participants’ quality of life after treatment. Evaluation will be performed at each post-operative visit by the Quality of Life in Epilepsy-89 scale (adults > 17 years) and the Quality of Life in Epilepsy-31 scale (children 4–16 years).Epilepsy-related medical costs at each post-operative visit.

### Statistical analysis

Statistical analysis will be mainly performed by researchers from Sanbo Brain Hospital, Capital Medical University, using the SAS 9.3 (SAS Institute Inc., Cary, NC, USA) software. Take the test level *α* = 0.05. The Kolmogorov-Smirnov test will be used to test whether the variables will be normally distributed. Measurement data conforming to normal distribution will express as mean ± standard deviation (‾X ± s), and measurement data not conforming to normal distribution will be expressed as interquartile range *M* (Q25, Q75). The *t*-test will be used to compare the normal distribution of continuous variables. The rank sum test will be used to compare the continuous variables that do not conform to the normal distribution. The chi-square test will be used to compare the categorical data. Univariate and multivariate methods will be used to analyze the preoperative and operative factors associated with seizure-free. Analysis of the primary outcome will be by intention-to-treat.

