## Methods/design

### General study design

A multicenter, randomized controlled, parallel-group clinical trial will be conducted at Sanbo Brain Hospital, Beijing Tiantan Hospital, and Xuanwu Hospital. This study has been registered in the Chinese Clinical Trial Registry before the enrollment of participants (http://www.chictr.org.cn, registration number: ChiCTR2200060974).

Participant baseline information will be collected approximately 10 days before surgery, including participant demographics, seizure status, use of ASMs, neurological status, electroencephalogram (EEG), and magnetic resonance imaging (MRI) findings. The perioperative information of the participants will be recorded based on the surgical records and anesthesia records, including length of operation, amount of bleeding, complications, and cost of operation. The participants will be followed up for three times at 3, 6, and 12 months after the operation. The timeline of this study is shown in Fig. 1. The baseline information mainly includes the following:Seizure condition: seizure frequency (time/month), seizure duration, severity, etc.Neurological impairment: neurological function physical examination and National Institutes of Health Stroke Scale (NIHSS) score.Use of anti-seizure medications: type and dosage of drugs.Preoperative EEG examination: scalp EEG spectrum distribution, EEG Epileptogenic Index, etc.Preoperative MRI.Quality of life: using the Quality of Life in Epilepsy-89 scale for adults (ages 17–60) and the Quality of Life in Epilepsy-48 scale for children (ages 14–16). Patients not in the above age range will not be assessed for quality of life.Cognitive function: using the Chinese version of the Wechsler Intelligence Scale-IV and the Chinese version of the Wechsler Development Scale-IV.

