### Randomization and blinding

Randomization will be performed by independent investigators with the SAS (9.3, SAS Institute Inc., Cary, NC, USA) software. The resulting list of random numbers has been placed into sequentially numbered, sealed, opaque envelopes. Based on the information obtained from the envelopes, consecutively enrolled participants will be randomly assigned, in a 1:1 ratio, to stereotactic lesioning or classical epileptogenic zone resective surgery. Patients who are assigned to stereotactic lesioning surgery will be also assigned in a 4:1 ratio to a subgroup of RF-TC and a subgroup of LITT. The same group of neurosurgeons at different centers (three groups in total) will be responsible for different procedures for each participant.

Researchers and clinical research coordinators participate in the grouping process. Clinical research coordinators are responsible for informing patients, but they are not involved in the patient assessment and treatment process. All subjects and clinicians will be aware of the trial group assignments before surgical treatment, outcome assessors. However, outcome assessors and statisticians will not be aware of the subgroups of subjects

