## Discussion

The randomized controlled trial can minimize the possible biases in the design and conduct of clinical trials. The conclusion of a well-designed and rigorously conducted randomized controlled trial is recognized as high-level evidence. To date, we have found no reports in the literature of randomized clinical trials of LITT and RF-TC for the treatment of focal DRE.

Epileptogenic focus resection is currently the most common and effective surgical treatment for focal DRE and is more likely to mean a radical cure. Among them, temporal lobectomy is the most common and has the best prognosis, while frontal lobectomy is the second most common [31–33]. Two randomized clinical trials of temporal lobe epilepsy found that patients treated with surgery were more likely to be seizure-free than those who continued medical therapy [28, 34]. However, it has been reported that resective surgery may lead to hemiplegia, memory impairment, visual field defect, and other complications [35, 36].

By selectively damaging a limited volume to the potential seizure initiation zone, stereotactic lesioning can limit the risk of neurologic impairment after surgery. However, despite the promising results, the seizure outcome after RF-TC and LITT is still not fully understood, with meta-analyses showing that seizure-free and responder rates varied widely across studies [25, 37, 38]. What is more, none of the studies included in the meta-analysis compared stereotactic injury with resective surgery. In addition, the predictors associated with postoperative outcomes remain unclear. Although some studies suggest that specific patient populations may achieve better outcomes, such as RF-TC-treated patients with periventricular nodular ectopia and LITT-treated patients with hypothalamic hamartoma. But to date, there have been few studies on the impact of the underlying etiology on the success rate of stereotactic lesioning. As mentioned above, there are still some deficiencies in the current research on stereotactic lesioning, which are the key issues of this study.

The protocol for this study was developed after careful discussion by MDT physicians in neurology, neurosurgery, neuroimaging, and neuropsychology. There was no patient or public involvement in the design of our study. We will do our best to perform our duties to provide reliable evidence for stereotactic lesioning in the treatment of epilepsy.

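### The arms are compared without covariates although centre, focus site and baseline seizure frequency are known before surgery: valid, but a small, avoidable loss of precision

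*Protocol article*

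**What the plan says.** All references are to the protocol article.

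- **Statistical analysis, group comparisons.** For normally distributed continuous data the t-test "will be used to compare the normal distribution of continuous variables". A rank sum test covers the rest, and "The chi-square test will be used to compare the categorical data". No covariate is named.
- **Statistical analysis, multivariable work.** The only such analysis is this: "Univariate and multivariate methods will be used to analyze the preoperative and operative factors associated with seizure-free". It is not described as the treatment comparison. The section adds: "Analysis of the primary outcome will be by intention-to-treat".
- **Primary outcome.** "The primary outcome is the participant’s seizure remission rate, which was defined by the following formula". The formula is a percentage fall from baseline, so baseline frequency is its denominator.
- **Randomization and blinding.** From an envelope list, "consecutively enrolled participants will be randomly assigned, in a 1:1 ratio, to stereotactic lesioning or classical epileptogenic zone resective surgery", then 4:1 to RF-TC or LITT within lesioning. No strata are mentioned. Each of the three centres has its own surgical group.
- **Discussion.** Among resections, "temporal lobectomy is the most common and has the best prognosis". No figure is given by focus site.
- **Sample size.** One-sided 95% interval, 10% limit, 20% withdrawal, 240 patients.

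Focus site is known early. A definite epileptogenic zone is an entry criterion, and the section on Arm 1 lets temporal or extratemporal focus decide the type of resection. Baseline seizure frequency is collected about 10 days before surgery.

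**The concern.** The article itself treats focus site as prognostic for resection and plans to model prognostic factors, yet leaves them out of the comparison that the trial exists to make. With no stratification stated, neither the allocation nor the analysis, as described, uses them.

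Two things are at stake. A noninferiority decision depends on where an interval ends relative to a limit, so unnecessary width costs power. And if covariates are not named in advance, an adjusted analysis could later be built around whichever imbalances appear.

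**Working it through.** **Plan figures.** 240 patients at 1:1 is 120 per arm; after 20% withdrawal, 120 × 0.8 = 96. The 240 itself cannot be rebuilt, because neither power nor the effective rate is stated. For noninferiority on equal rates at one-sided 0.05, 80% power and a 10-point limit, 240 would require a rate of about 91.5%.

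**Assumptions.** The documents give neither the temporal share nor the outcome gap. I take a share f = 0.5 and gaps of 10 to 30 points in seizure freedom. The 30 is an outer bound: the Background quotes seizure freedom of 50 to 80% after surgery, not split by focus. I apply the 10% limit to seizure freedom for illustration only, because the article ties it to no outcome.

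**Step 1: chance imbalance.** The SD of the between-arm difference in temporal share is √(2f(1−f)/n) = √(0.5/96) = 0.072. The 95% limit is 1.96 × 0.072 = 0.14, or 14 points.

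**Step 2: shift in the seizure-free difference.** Shift = imbalance × gap. The average absolute shift is 0.80 × SD × gap.

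**Step 3: gain from adjusting for focus.** With an overall rate of 65%, the unadjusted variance term is 0.65 × 0.35 = 0.2275. The within-focus term at 80%/50% is (0.16 + 0.25)/2 = 0.205, and 1 − 0.205/0.2275 = 9.9%. Power = Φ(0.10/SE − 1.645), with SE = √(2 × term/96). At 80%/50% the SE is 6.88 points unadjusted and 6.54 adjusted.

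| Assumed rates, temporal / extratemporal | Gap (points) | Average shift | 95% limit | Variance cut | Power, unadjusted to adjusted |
|---|---|---|---|---|---|
| 70% / 60% | 10 | 0.6 | 1.4 | 1.1% | 42.4% to 42.7% |
| 75% / 55% | 20 | 1.2 | 2.8 | 4.4% | 42.4% to 43.7% |
| 77.5% / 52.5% | 25 | 1.4 | 3.5 | 6.9% | 42.4% to 44.4% |
| 80% / 50% | 30 | 1.7 | 4.2 | 9.9% | 42.4% to 45.4% |

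With 120 per arm, the 95% limit runs from 1.3 to 3.8 points.

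**Step 4: simulation.** In 400,000 simulated trials (80%/50%, 96 per arm), one-sided type I error was 0.050 unadjusted and 0.051 adjusted. Power was 41.7% and 45.8%.

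**Step 5: if focus matters only after resection.** With equal arms, the shift is the imbalance times the mean of the two arms' gaps. A zero gap after lesioning therefore halves the 95% limits, to about 0.7 to 2.1 points.

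**Step 6: LITT against resection.** One fifth of 120 is 24, and 24 × 0.8 is about 19. With f = 0.6, the SD is √(0.24 × (1/19 + 1/96)) = 0.123. The 95% limit is 24 points of imbalance, or 6.0 points of shift at a 25-point gap. With f = 0.5 and gaps of 10 to 30, it is 1.96 × √(0.25 × 0.0630) × gap, or about 2.5 to 7.4 points.

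**Step 7: the primary outcome.** Simulation with 192 patients (4,000 trials per scenario, adjusted against unadjusted least squares) gave a variance cut of about 0 to 4% for the percentage-change score. Since √0.96 = 0.98, the interval narrows by at most about 2%. With uninformative covariates the loss was 1 to 3%. This agrees with the approximation k/(N − k − 3) = 4/185 = 2.2% for two centre terms, focus and log frequency.

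**The case against.** Several objections are sound and set the limits of the point.

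- **The unadjusted test is valid.** A reader might infer that imbalance in focus biases the result. It does not: the unadjusted interval already allows for it, and type I error is about 5% either way.
- **A reader might infer a shift of about a third of the 10% limit.** That needs an assumed gap of about 25 points and an imbalance at the 95% limit. At that gap the average shift is 1.4 points, and the chance of exceeding 3.33 points is 6.5% (96 per arm) or 3.9% (120 per arm). It also sets a seizure-free difference against a limit that Sample size links to no outcome.
- **The primary outcome gains little.** Its denominator is already baseline frequency, and most of the benefit falls on seizure freedom and Engel class.
- **Prognostic support is thin.** The Discussion's statement concerns resection. For lesioning it says that predictors of outcome are not established. Nothing shows that centre or baseline frequency is prognostic.
- **The article is condensed.** A fuller protocol or an analysis plan may name covariates or strata, so their absence here does not show that the trial has none.

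What remains is that the article does more than stay silent. It names specific tests, none of which takes a covariate, and reserves multivariable methods for another question. A better comparison is available from data already collected.

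**Conclusion.** The point holds as a minor gain in precision and prespecification. For seizure freedom, adjusting for focus cuts variance by about 1 to 10% over assumed gaps of 10 to 30 points. At the top of that range power rises from about 42% to 45 or 46% against a 10-point limit. This is equivalent to 192/0.901 = 213 evaluable patients instead of 192; at the bottom of the range it is about 2 extra patients. For the percentage-change primary outcome the gain is about 0 to 4%.

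These sizes rest on an assumed temporal share and assumed gaps. They would be smaller if focus does not predict outcome after lesioning. The documents do not support a claim of bias, of an invalid test or of a typical shift near a third of the limit.

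**What to change.** In Statistical analysis, prespecify the following, or confirm that the full analysis plan already does so:

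- **Seizure freedom and Engel class I:** a standardised risk difference with confidence interval, from a logistic model with arm, centre, focus site (temporal or extratemporal) and log baseline seizure frequency. Entry requires at least one seizure a month, so the logarithm is always defined.
- **Seizure remission rate, at each planned visit:** an estimate adjusted for the same covariates with bootstrap or robust intervals. If the score is skewed, use a rank test stratified by centre and focus. Skew is likely, because the score has a ceiling of 100% and no lower bound.
- **Sensitivity analysis:** the unadjusted results.

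The cost is slightly more analysis work, and a loss of about 1 to 3% of variance if the covariates prove uninformative. No new data are needed, and four covariate terms are few for about 192 patients. The model-based estimates also supply the interval that Sample size relies on, which rank sum and chi-square tests alone do not.

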## Background

Epilepsy is a common disease of the nervous system causedby different causes, with spontaneous, recurrent, and unpredictable seizures as the main characteristics. It also has numerous neurobiological, cognitive, and psychosocial consequences [1]. Several epidemiological studies show that the incidence of epilepsy is 5.5–7.3‰ [2–4]. Drug therapy is the preferred treatment for epilepsy at present. However, about 30% of patients are still unable to control their seizures after continuous treatment with two or more appropriate anti-seizure medications (ASMs), which are defined as drug-resistant epilepsy (DRE) [5, 6]. In cases of drug failure, optimal seizure control usually requires neurosurgical intervention targeting the epileptic foci. Epilepsy surgery can be divided into diagnostic surgery (subdural electrode implantation, stereotactic multicontact electrode implantation, etc.), resective surgery (lesion resection, lobectomy, hemispherectomy, etc.), and palliative neuromodulation surgery (vagus nerve stimulation, deep brain stimulation, etc.) [7–9]. Patients with drug-resistant focal epilepsy can benefit from the removal or disconnection of a circumscribed brain region to achieve complete seizure control or at least reduce disabling seizures. Among carefully selected patients, the proportion of individuals who are seizure-free after surgery ranges from 50 to 80% [10, 11].

In the 1960s, Talairach and Bancaud innovatively took the anterior and posterior connections of the brain as the benchmark for homogenization, which created the stereotactic surgery technique in neurosurgery [12]. In recent years, with the rapid development of robot-assisted technology, the stability, accuracy, and economy of stereotactic surgery have made great progress. With the assistance of a robot, the implantation time of multicontact electrodes has been shortened to 3–5 min per electrode, and the accuracy of entry point, angle, and other parameters has been significantly improved; thus, the safety of surgery has been improved [13, 14]. Today, stereoelectroencephalography (SEEG) provides a unique approach to exploring the pathophysiology of epilepsy and pinpointing the epileptogenic network that no other noninvasive examination can provide. At the same time, because of the advantages of nerve function protection, stereotactic lesioning accounts for an increasing proportion of surgical treatment in major epilepsy medical centers around the world.

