### Sample size

According to earlier studies and the previous work of our research team, the effective rates of stereotactic EEG-guided RF-TC, MRI-guided stereotactic LITT, and resective surgery are similar, and the rates of postoperative neurological impairment are 2%, 2%, and 11%. We expect to use a one-sided 95% confidence interval, a noninferiority limit of 10%, and an expected withdrawal rate of 20%. Therefore, we expect to enroll a total of 240 patients in this study. Patients will be recruited from outpatient and MDT with strict inclusion criteria.

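### The trial is planned for noninferiority with a 10% limit, but the analysis section names only tests of difference and gives the primary outcome no interval, margin or decision rule

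*Protocol article*

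**What the plan says.** **Sample size.** The protocol article states: "We expect to use a one-sided 95% confidence interval, a noninferiority limit of 10" per cent. It adds an expected withdrawal rate of 20% and a total of 240. On efficacy its premise is that "the effective rates of stereotactic EEG-guided RF-TC, MRI-guided stereotactic LITT, and resective surgery are similar". It gives no value for those rates, does not define them, and does not say which outcome or comparison the limit belongs to.

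**Statistical analysis.** α is 0.05, with no sidedness. "The Kolmogorov-Smirnov test will be used to test whether the variables will be normally distributed". Normal variables go to a t-test. For the rest, "The rank sum test will be used to compare the continuous variables that do not conform to the normal distribution". Categorical data go to a chi-square test. The primary outcome is analysed by intention-to-treat. The section mentions neither noninferiority, nor the limit, nor a confidence interval for the treatment difference.

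**Primary outcome.** This is the percentage fall from baseline in each participant's monthly seizure frequency. The section names no time point. The Abstract and Table 1 give three (3, 6 and 12 months).

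**The concern.** A noninferiority claim needs an estimate of the difference and a confidence limit to set against the margin. The listed tests ask another question: whether the data are incompatible with no difference at all. A significant result does not show that the deficit exceeds the margin, and a non-significant one does not show that it is smaller.

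This matters here because a real deficit is plausible on the protocol's own words. The Abstract says that seizure freedom is less likely with the two lesioning procedures, while the Sample size section assumes similar effectiveness. If lesioning is somewhat worse, the named tests may well not detect it, and the analysis section gives no other basis for a conclusion.

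**Working it through.** **1. Evaluable numbers.** 240 × (1 − 0.20) = 192. With 1:1 allocation of lesioning to resection (Randomization and blinding), that is 96 per arm.

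**2. The plan's own figure.** The total of 240 could not be rebuilt, because neither power nor an effective rate (or SD) is stated. The nearest variant using stated rates is superiority on neurological impairment, 11% v 2%, one-sided 0.05, with 80% power assumed: 92 per arm, and 184 / 0.8 = 230. That is a secondary outcome and a different hypothesis, so it does not settle what the 10% refers to.

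**3. The two sections side by side.**

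| | Sample size | Statistical analysis |
|---|---|---|
| Question | Noninferiority | Difference |
| Tool | One-sided 95% interval | t, rank-sum or chi-square test |
| Limit | 10% | None |
| Scale | Effective rates (undefined) | Whatever type the variable has |

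**4. The rank-sum route.** The outcome cannot exceed 100%, and every seizure-free participant scores exactly 100%, so non-normality is likely and the rank-sum test would then apply. Its p-value has no units to compare with 10%. The usual companion estimate, the median of all pairwise differences, does not help when ties are heavy. Assume 65% of the resection arm and 55% of the lesioning arm are at 100%:
- both members of a pair at the cap: 0.65 × 0.55 = 0.3575 (difference exactly 0)
- resection only: 0.65 × 0.45 = 0.2925
- lesioning only: 0.35 × 0.55 = 0.1925
- neither: 0.35 × 0.45 = 0.1575, taken as split evenly

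Pairs favouring resection: 0.2925 + 0.0788 = 0.371. Pairs favouring lesioning: 0.1925 + 0.0788 = 0.271. Both are below 0.5, so the estimated shift is 0 although the seizure-free proportions differ by 10 points.

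**5. Continuous outcome, true deficit of 10 points.** The SD is not stated, so a range is assumed. SE = SD × √(2/96).
- P(difference test non-significant) = 1 − Φ(10/SE − 1.96)
- Noninferiority power if the arms are truly equal = Φ(10/SE − 1.645)

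| SD | SE | Non-significant at a true deficit of 10 | Noninferiority power, equal arms |
|---|---|---|---|
| 25 | 3.61 | 21% | 87% |
| 28 | 4.04 | 30% | 80% |
| 30 | 4.33 | 36% | 75% |
| 40 | 5.77 | 59% | 54% |
| 50 | 7.22 | 72% | 40% |

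**6. Proportion, true deficit of 10 points.** With p̄ the mean of the two rates, SE₀ = √(2p̄(1 − p̄)/96) and SE₁ = √((p₁(1 − p₁) + p₂(1 − p₂))/96). P(non-significant) = 1 − Φ((0.10 − 1.96·SE₀)/SE₁). For 80% v 70%: SE₀ = 0.0625, SE₁ = 0.0621, result 64%. For 70% v 60% it is 70%; for 60% v 50% and for 50% v 40% it is 72%.

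**7. The noninferiority test in the same situations.** With the true deficit equal to the limit, the pass probability is Φ(0 − 1.645) = 5% by construction.

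**8. Noninferiority power on a proportion, equal true rates.** Power = Φ(0.10/√(2p(1 − p)/96) − 1.645). At 50%: 0.10/0.0722 = 1.386, power 40%. At 60%: 41%. At 70%: 45%. At 80%: 0.10/0.0577 = 1.732, power 54%. For 80% power with 20% withdrawal, the total would be 775 at a rate of 50% and 495 at 80%.

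**The case against.** The strongest reply is that the interval in the Sample size section is the intended decision rule, that the Statistical analysis section is a generic list for all variables in a condensed article, and that an unseen analysis plan may supply the rest. The t-test route also yields an interval directly. Part of this stands: the intention may well be right. But the analysis section does not merely stay silent. It names the tests and the criterion for choosing between them, and these do not answer the question for which the trial was sized. On the rank-sum route no usable interval follows.

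Three stronger readings are tempting, and the document does not support them.
- A reader might infer that the investigators will take a non-significant result as proof that lesioning is as effective as resection. No section says so. The risk arises because no other rule is given.
- A reader might take the Background statement that "the proportion of individuals who are seizure-free after surgery ranges from 50 to 80" per cent as this trial's expected share at the 100% cap. It is a literature range for selected surgical patients, and the Abstract expects less of lesioning. It serves above only as an assumed range.
- A reader might fault the tests for leaving out centre, focus location and baseline frequency. Under randomisation an unadjusted comparison is valid, so adjustment is a preference and not a correction.

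It is also fair to say that a single figure of about 70% non-significant would overstate the matter. It belongs to a proportion, whereas the stated outcome is continuous and its result depends on an unknown SD.

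**Conclusion.** The point holds as a conflict between two sections. The planned hypothesis is noninferiority with a 10% limit, the written analysis cannot establish it, and the limit has no defined scale. With 96 evaluable per arm and a true deficit equal to the limit, a difference test would miss the deficit in about 21–72% of trials on the continuous outcome, or 64–72% on a proportion. The noninferiority test would pass about 5%. These sizes rest on assumed SDs of 25–50 points, assumed control rates of 50–80% and normal approximations; the conflict itself rests on none of them. It must be put right, because the primary conclusion depends on it.

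**What to change.** Before outcome data are compared, state in the Statistical analysis section:
- The primary comparison is lesioning minus resection on the outcome as defined under Primary outcome, at one named time point.
- The estimate is the difference in mean percentage reduction, with a one-sided 95% lower confidence bound (for example by bootstrap, since the outcome is capped at 100%).
- Noninferiority is concluded only if the bound lies above −10 points.
- The rank-sum test is supportive, and a per-protocol analysis is reported beside intention-to-treat.

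If the sponsor meant the 10% for a success proportion, the Primary outcome and Sample size sections must be reconciled by a formal amendment that defines that proportion. The plan should then state that power with 240 enrolled is about 40–54% for equal true rates of 50–80% (assumed).

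**Cost.** More analysis wording and some programming. Recruitment is under way, so the change needs ethics review and, if it counts as important, Health Commission approval (Ethics and communication). The stated power may look less favourable: on the continuous scale it is about 80% only if the SD is near 28 points. The mean is also sensitive to worsening, because the outcome has no lower bound. A participant going from 1 to 5 seizures a month scores (1 − 5)/1 = −400%. Compared with a score of 100%, that moves a 96-person arm mean by 500/96 = 5.2 points, so the handling of such values should be fixed in advance.
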